### Adherence, modifications, and concomitant care

In both groups, the importance of attendance and commitment to the meetings will be discussed. It will also be emphasized that it will be a safe space for listening, welcoming, and confidentiality. Participants will be asked about their feelings and doubts about their study process. The meetings will always occur on the same predetermined day, time, and location. Participants will be notified via smartphone before each meeting as a reminder. To increase adherence and commitment to the study, participants will also be offered activities to practice at home, such as food records, observation, and reflection exercises, or they will be asked to bring materials related to the next meeting (e.g., food packaging).

Adherence to the proposed interventions will be checked at each meeting. However, the difficulty of carrying out what is proposed does not compromise remaining in the group meetings.

Participants cannot change the group they have been allocated to. However, they are free to leave the study as they wish. The meeting protocol for both groups cannot be modified, as this could bias the study.

### Outcomes

#### Primary outcomes.

Body dissatisfaction will be assessed using the Body Shape Questionnaire (BSQ), translated to Portuguese [36], which is used to identify concerns about body shape and self-deprecation related to physical shape. It has 34 questions related to body image, with a scale from 1 to 6: 1-Never, 2-Rarely, 3-Sometimes, 4-Frequently, 5-Very Often, and 6-Always. The result is obtained by adding up all the scores. A score of less than 80 points means that the individual has no dissatisfaction. Between 80 and 110, there is mild dissatisfaction; between 111 and 140, moderate dissatisfaction, and over 140 severe dissatisfaction.

Dysfunctional eating behavior will be assessed using the instrument “The three-factor eating questionnaire - R21 (TFEQ-R21)” [37], a questionnaire developed to evaluate the eating behavior of obese and eutrophic individuals, translated and validated to Brazilian [38]. The instrument consists of 21 questions, with questions 1–20 having 4 alternatives (scoring from 1 to 4, from the highest severity of dysfunctional eating to the lowest) and the last question having a scale from 1 to 8 (from the lowest degree of food restriction to the highest). Three dimensions of eating behavior are assessed: cognitive restriction, uncontrolled eating and emotional eating. Cognitive restriction refers to a set of self-imposed food obligations and prohibitions in order to lose or maintain weight. However, when there is a limitation on food consumption, both qualitatively and quantitatively, these individuals, in certain situations such as exposure to a forbidden food, lose self-control and tend to overeat with or without the presence of hunger, characterizing uncontrolled eating. Finally, emotional eating refers to emotions influence on food intake, which can lead to less healthy choices. It is an appropriate instrument for its purpose and serves to support an approach that values the behaviors resulting from poor eating, such as external stimuli and emotions [38]. The higher the score, the more dysfunctional the behavior.

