#### Secondary outcome.

Self-compassion levels: the Self-Compassion Scale (SCS) will be used, with 26 items, which was developed to measure self-compassion in three components: self-judgment versus self-kindness, sense of isolation versus common humanity and hyper-identification versus mindfulness [39]. The items are grouped into six subscales: Self-kindness (items 5, 12, 19, 23, 26); Self-judgment (items 1, 8, 11, 16, 21); Common Humanity (items 3, 7, 10, 15); Isolation (items 4, 13, 18, 25); Mindfulness (items 9, 14, 17, 22) and Over-identification (items 2, 6, 20, 24). Each item is rated on a 5-point Likert scale (1 = Almost never; 5 = Almost always). The total score is obtained from the average of the six subscales. Higher scores mean more self-compassion.

Sociodemographic characteristics: to gather information on the participants’ characteristics, an anamnesis form will be used, in which the participants will fill out questions on sociodemographic issues (name, age, gender, marital status and income, education), as well as general health and lifestyle questions such as: physical activity, smoking, alcohol use, psychological support, perceptions about the body and diet and any other information that the participant can provide to better conduct the research.

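### The TFEQ-R21 scoring rule contradicts its own interpretation: items 1–20 are coded from worst (1) to best (4), yet a higher score is read as worse, with no recoding stated

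*Protocol article*

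**What the plan says.** All the relevant TFEQ-R21 text is in one paragraph of the protocol article, under Primary outcomes.

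- Items 1–20 have four alternatives, described as "scoring from 1 to 4, from the highest severity of dysfunctional eating to the lowest". Read as codes, 1 is the most dysfunctional answer and 4 the least.
- Item 21 is described as "the last question having a scale from 1 to 8 (from the lowest degree of food restriction to the highest". Here a larger number means more restriction, and the paragraph treats cognitive restriction as one of the three dimensions of dysfunctional eating.
- The interpretation of the score is "The higher the score, the more dysfunctional the behavior".

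The paragraph names three dimensions (cognitive restriction, uncontrolled eating, emotional eating) but refers only to a single undefined score. By contrast, the Body Shape Questionnaire has an explicit sum rule in the same section.

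The Self-Compassion Scale (SCS) is described under Secondary outcome. Items are coded by frequency: "Each item is rated on a 5-point Likert scale (1 = Almost never; 5 = Almost always". The components are set out as opposed pairs: "self-judgment versus self-kindness, sense of isolation versus common humanity and hyper-identification versus mindfulness". The total is defined by "The total score is obtained from the average of the six subscales. Higher scores mean more self-compassion". Reversal of the negative subscales is neither stated nor ruled out.

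**The concern.** The TFEQ-R21 paragraph gives a coding and an interpretation that point in opposite directions, and no step that connects them. This is more than detail left to a fuller document, because two printed statements about the same score disagree.

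The sign of a primary outcome is at stake. The Discussion states a directional hypothesis: the self-compassion approach should reduce dysfunctional eating more than the diet approach. If the codes are stored as printed, left unreversed, and read by the printed interpretation, a benefit on items 1–20 appears as harm and the favoured arm changes.

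The planned analysis would not expose the mistake. The group-by-time test gives the same p-value whether a score made only of items 1–20 is reversed or not. The article also says the statistical analysis is blinded, so an analyst without group labels has little chance of noticing an implausible direction.

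Item 21 raises a second problem. Because it runs against the other items as printed, a score that contains both loses information as well as direction.

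**Working it through.** The article prints no TFEQ-R21 range, total or example, so there is no TFEQ figure to reproduce. The sample size of 76 does not depend on scoring. A two-sided t-test with d = 0.7, 5% significance and 80% power gives 33.02, hence 34 per arm; 34/0.9 = 37.8, hence 38 per arm and 76 in total, as stated.

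**Inputs (Primary outcomes).** Items 1–20: 1 = most severe, 4 = least severe. Item 21: 1 = least restriction, 8 = most restriction. Stated reading: higher = worse.

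**Check 1: direction of a total.** A simple sum is assumed, because no aggregation rule is printed.

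| Respondent | Codes as printed | Items 1–20 reversed (5 − raw) |
|---|---|---|
| Most dysfunctional | 20×1 + 8 = 28 | 20×4 + 8 = 88 |
| Least dysfunctional | 20×4 + 1 = 81 | 20×1 + 1 = 21 |

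As printed, the higher score belongs to the least dysfunctional respondent, which contradicts the stated reading. After reversal the two agree. The distance between the extremes is 81 − 28 = 53 as printed and 88 − 21 = 67 when aligned. The loss of 14 is twice the 7-point span of item 21, which pulls the wrong way.

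**Check 2: direction of a score without item 21.** For k items, all from 1–20, the printed codes give k×1 at the worst and k×4 at the best. The direction is again opposite to the stated reading. Reversal gives 5k minus the raw sum, which is linear: it changes the sign of a group difference but not its size or its p-value.

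**Check 3: a restriction score with item 21.** The article does not print which items belong to which dimension, so let k be the number of restriction items among 1–20. As printed, most restricted = k + 8 and least restricted = 4k + 1, so the extremes differ by 3k − 7. Aligned, they differ by 3k + 7.

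| k (assumed) | Most restricted, as printed | Least restricted, as printed | Difference as printed | Difference aligned |
|---|---|---|---|---|
| 3 | 11 | 13 | 2 | 16 |
| 6 | 14 | 25 | 11 | 25 |

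Over this range the score points the wrong way and loses much of its ability to separate respondents. Here reversal is not a mere change of sign.

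**Check 4: illustration of the sign.** A simulation assumed a latent benefit of 0.7 SD for self-compassion, a simple sum, and item 21 moving with the same latent trait. Self-compassion minus diet was +5.5 points (d about +0.62) on the printed codes and −6.7 points (d about −0.63) with items 1–20 reversed. On the printed codes and the printed reading, a true benefit is called harm.

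**Check 5: the SCS.** Let p be the common score on the three positive subscales and n that on the three negative ones. Without reversal the total is (3p + 3n)/6, so the profiles (5,1), (3,3) and (1,5) all give 3.0. With reversal it is (3p + 3(6 − n))/6, which gives 5.0, 3.0 and 1.0. Only the reversed total fits the stated reading of the scale.

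**The case against.** The strongest reply is that the parenthesis on items 1–20 may describe the order in which the response options appear, while the closing sentence describes the scored instrument. The article cites the questionnaire and its Brazilian validation, and a team that follows that published scoring would obtain the intended direction. For any score made only of items 1–20, the worst outcome is then a mislabelled direction, which is put right in the scoring syntax without new data. Design, data collection and sample size are untouched. The 21-item sum is also an assumption, since the article names three dimensions and defines no total.

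Much of this stands. It makes the reversal conditional and removes any claim that the trial will report a wrong result. It does not remove the contradiction. The article's word is scoring, and if only option order was meant, the sentence still needs correcting. The reply about linear reversal also does not cover a score that contains item 21.

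A reader might further infer that the SCS total averages positive and negative subscales without reversal and so loses its meaning. The article does not support that. It is silent on reversal; its opposed pairs and its stated reading of the total both imply that reversal is intended, and a condensed article may leave that step to the cited scale. The 3.0 result in Check 5 shows what an unreversed average would do, not what the plan prescribes.

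A reader might also infer that a TFEQ total must not be used. That would be a preference about the outcome and does not follow from the coding contradiction.

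**Conclusion.** The point holds for the TFEQ-R21. The protocol article contradicts itself on a primary outcome: 20 of 21 items are coded against the stated interpretation, item 21 is coded with it, and no recoding is given.

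The consequence is conditional. If the printed codes are what is stored, and they are analysed without recoding and read as printed, the direction of the result is reversed: 28 against 81 for the extreme respondents, where 88 against 21 is intended, on an assumed simple sum. Scores that combine item 21 with unreversed items are distorted as well; how far depends on the item-to-dimension map, which the article does not print.

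The documents do not show that the team will score the questionnaire this way. The correction is still worth making, because the printed rule for a primary outcome is wrong as it stands and the planned test would not reveal the error. The SCS matter is a minor clarification on a secondary outcome.

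**What to change.** - **Primary outcomes, TFEQ-R21 paragraph:** rewrite it so that item direction and interpretation agree. If the stored codes are as printed, state that items 1–20 are reversed (5 minus raw) and that item 21 is aligned with the restriction items before scoring, following the cited validated scoring. If the parenthesis described only the order of the response options, say so and give the codes actually assigned.
- **Same paragraph:** state whether the three dimension scores or a total is the primary TFEQ-R21 outcome.
- **Scoring syntax:** check the SPSS recoding against the codes stored from Google Forms before any outcome analysis. Scoring one fictitious most-dysfunctional and one least-dysfunctional record would confirm the direction.
- **Secondary outcome, as a minor clarification:** add that the self-judgment, isolation and over-identification items are reversed before the six SCS subscales are averaged.

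The cost is a few sentences and one check of the syntax. No new data are needed, and the sample size does not change.

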#### Secondary outcome.

Self-compassion levels: the Self-Compassion Scale (SCS) will be used, with 26 items, which was developed to measure self-compassion in three components: self-judgment versus self-kindness, sense of isolation versus common humanity and hyper-identification versus mindfulness [39]. The items are grouped into six subscales: Self-kindness (items 5, 12, 19, 23, 26); Self-judgment (items 1, 8, 11, 16, 21); Common Humanity (items 3, 7, 10, 15); Isolation (items 4, 13, 18, 25); Mindfulness (items 9, 14, 17, 22) and Over-identification (items 2, 6, 20, 24). Each item is rated on a 5-point Likert scale (1 = Almost never; 5 = Almost always). The total score is obtained from the average of the six subscales. Higher scores mean more self-compassion.

Sociodemographic characteristics: to gather information on the participants’ characteristics, an anamnesis form will be used, in which the participants will fill out questions on sociodemographic issues (name, age, gender, marital status and income, education), as well as general health and lifestyle questions such as: physical activity, smoking, alcohol use, psychological support, perceptions about the body and diet and any other information that the participant can provide to better conduct the research.

### Sample size

Considering the study by Albertson, Neff and Dill-Shackleford (2014) [40], which found an improvement in body dissatisfaction from meditation based on self-compassion techniques with an effect size of 0.73 (high), a sample size of 76 people (38 for each group) was calculated. This calculation considered a power of 80%, a significance level of 5% and a Cohen’s d of 0.7 to test whether there is a minimal difference in the body dissatisfaction averages and self-compassion levels between the intervention and control groups, already including an addition of 10% for possible losses and refusals.

### Randomization, allocation and masking of groups

Participants will be randomized to the Self-Compassion or Diet group with 1:1 allocation in the Random Group Generator (https://pt.rakko.tools/tools/59/). The nutritionists responsible for applying the interventions will have no contact with the randomization and will not know in advance who will go to which group, only the research coordinator.

Due to the nature of the intervention, it is not possible to blind the researchers and participants during the study’s conduction after the randomization process. However, the intervention and control groups will not interact in any way. Likewise, the statistical analysis will be blinded to the evaluator.

### Statistical analysis

Baseline characteristics of the participants will be compared between groups (self-compassion and diet). For categorical variables, the Pearson Chi-square test will be used, with continuity correction for dichotomous variables or Fisher’s exact test when at least one cell has an expected count of less than five. For continuous numerical variables, the Shapiro-Wilk test will assess normality. If normality is accepted, results will be presented as mean and standard deviation and analyzed using Student’s t-test for independent samples. If the distribution is non-parametric, data will be expressed as median and interquartile range and analyzed using the Mann-Whitney U test. No significant differences between groups at baseline are expected due to the randomization process, which should provide similar groups. However, if significant differences are observed, these variables will be included as adjustments in multivariable analyses, as described below for primary and secondary outcomes.

Comparisons between baseline and follow-up for the primary and secondary outcomes will be tested using a General Linear Model (GLM) for repeated measures, considering the interaction between group (self-compassion and diet) and time (before and after). Separate analyses will be conducted for each follow-up point: from baseline to the end of the 8-week intervention, from baseline to 3 months after the intervention, and from baseline to 6 months after the intervention. Differences will be considered statistically significant at p < 0.05. The data will be analyzed using Statistical Package for the Social Sciences (SPSS) software, version 26.0.

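### The two-visit repeated-measures test is a change-score comparison with significance-triggered covariates; always adjusting for the baseline score is more precise and needs no new data

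*Protocol article*

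**What the plan says.** The relevant text is in the Statistical analysis and Sample size sections of the protocol article.

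- **Model.** "Comparisons between baseline and follow-up for the primary and secondary outcomes will be tested using a General Linear Model (GLM) for repeated measures". The effect of interest is the group-by-time term, where time has only two levels, before and after. The section then specifies separate analyses from baseline to the end of the 8-week intervention, to 3 months and to 6 months.
- **Covariates.** Baseline characteristics are tested between groups. The section expects no significant differences because of randomisation, but it adds this rule: "if significant differences are observed, these variables will be included as adjustments in multivariable analyses".
- **Sizing.** The trial assumes 80% power and a 5% level. The effect size is given as "Cohen’s d of 0.7 to test whether there is a minimal difference in the body dissatisfaction averages"; the self-compassion score is named alongside. The result is "a sample size of 76 people (38 for each group) was calculated". The allowance for attrition is described as "already including an addition of 10% for possible losses and refusals". The section gives neither a baseline/follow-up correlation nor the SD in which d is expressed.

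These are positive statements of method, so the point does not depend on anything the article may have left to a fuller document.

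**The concern.** Baseline scores are collected on every scale, but by default the planned model uses them only by subtraction. Subtraction fixes the baseline slope at 1. Unless the true slope is 1, this adds noise and carries part of any chance baseline difference into the treatment estimate.

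The covariate rule does not repair this. After randomisation, a significant baseline difference is a chance event, so the rule lets chance decide which model is fitted. It also passes over prognostic variables whose gaps fall short of significance. What is at stake is precision and a fully prespecified model.

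**Working it through.** **Inputs.** From the article: d = 0.7, 80% power, 5% level, 38 per arm including 10% for losses, 1:1 allocation, and a two-level group-by-time test. Assumed: a two-sided test, equal SDs at both visits (set to 1), and rho from 0.3 to 0.7.

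**1. The plan's own figure.** A two-sample t-test with d = 0.7 needs 34 per arm (power 81.2%). Allowing for losses, 34/0.9 = 37.8 and 34 x 1.1 = 37.4 both round up to 38 per arm, 76 in total. The stated sample size reproduces. Conversely, 38 x 0.9 = 34.2, so 34 per arm is the evaluable number used below.

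**2. What the planned test is.** With two visits, the group-by-time test is the t-test on follow-up minus baseline. On one simulated data set, the change-score t-test and a mixed model with a free group-by-time term both gave t = 4.425. Adding the baseline score as a covariate to the change model gave t = 4.927, the same as ANCOVA.

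**3. Efficiency.** Var(change) = 2(1-rho). Var(ANCOVA residual) = 1-rho². The ratio ANCOVA/change is (1-rho²)/[2(1-rho)] = (1+rho)/2, which is below 1 for every rho < 1. This ignores the small cost of estimating the slope.

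**4. Power if d is in follow-up SD units.** Noncentral t with noncentrality (0.7/√variance) x √(34/2), on 66 df for change and 65 df for ANCOVA:

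| rho | Variance, change / ANCOVA | Ratio | Power, change | Power, ANCOVA | n per arm for 80%, change / ANCOVA |
|---|---|---|---|---|---|
| 0.3 | 1.40 / 0.91 | 0.65 | 67.1% | 84.6% | 46 / 31 |
| 0.5 | 1.00 / 0.75 | 0.75 | 81.2% | 90.7% | 34 / 26 |
| 0.7 | 0.60 / 0.51 | 0.85 | 95.6% | 97.8% | 21 / 18 |

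At rho 0.8 the figures are 99.4% and 99.7%. The planned test falls below 80% only when rho is below about 0.5.

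**5. Power if d is in change-score SD units.** The noncentrality of the planned test is 0.7 x √17 = 2.89 whatever rho is, so power stays at about 81%. The variance ratio in step 3 is unchanged, so ANCOVA remains the more precise analysis.

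**6. Effect of the trigger.** It was applied to the baseline outcome in 10,000 simulated trials per setting, with d in follow-up SD units. Power was 68.3%, 82.2% and 96.0% at rho 0.3, 0.5 and 0.7, against 84.0%, 90.6% and 97.8% for ANCOVA always. The trigger recovers little. With no true effect, rejection rates for all three approaches lay between 3.8% and 5.3%.

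**7. Over-correction given a chance gap.** With a baseline gap g, the change score estimates the effect minus (1-rho) x g.

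- SE of the gap: √(2/34) = 0.243 SD.
- Median absolute gap: 0.6745 x 0.243 = 0.16 SD. At rho 0.5 the shift is 0.5 x 0.16 = 0.08 SD, about 12% of 0.7.
- Largest gap that triggers nothing: t(0.975, 66) x 0.243 = 0.48 SD. At rho 0.5 the shift is 0.24 SD, about a third of 0.7. At rho 0.7 it is 0.3 x 0.48 = 0.15 SD.

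**The case against.** The strongest reply is that the planned test is valid and may be amply powered. Over repeated randomisations the change score is unbiased and its type I error is not inflated. At rho 0.7 the loss is about two points of power. Rho is not in the article, so no shortfall can be asserted. All of this stands, and it limits the point to efficiency and prespecification.

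Several stronger readings are tempting, but the document does not support them:

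- **That the trial misses its 80% power.** This needs rho below about 0.5 and d in follow-up SD units. The reference to averages favours that unit, but the benchmark of 0.73 is described as an improvement, so the unit is not settled.
- **That chance imbalance is left uncorrected.** For the baseline outcome score, the change score corrects too much. If that score is among the variables tested and differs significantly, the rule enters it and the test becomes ANCOVA. Uncorrected describes only other prognostic variables with non-significant gaps.
- **That any mixed model would be better.** On complete two-visit data, a mixed model with baseline as a response and a free group-by-time term gives the same test. The gain comes from baseline adjustment, or from partly missing follow-up.
- **That 0.24 SD is the typical distortion.** It is the boundary case, and chance produces a larger gap only 5% of the time.

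The benefit from partly missing follow-up is also limited under the plan as written. The Data management section excludes all data from women who discontinue or deviate, and the Recruitment section makes 75% attendance a condition of staying in the study. An all-visit model would then help mainly with women who remain in the study but miss a questionnaire. That exclusion rule is a separate matter.

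**Conclusion.** The point holds as an avoidable loss of precision in a valid test, together with a covariate rule that lets chance choose the model. With equal SDs, ANCOVA's residual variance is (1+rho)/2 of the change-score variance: 0.65 to 0.85 over rho 0.3 to 0.7. If d is in follow-up SD units with 34 evaluable per arm, the gain is about 17 points of power at rho 0.3, 9 to 10 at 0.5 and 2 at 0.7.

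The efficiency ordering and the weakness of the trigger can be stated with confidence. The size of the power loss cannot, because it depends on rho and on the SD behind d. A reader might infer that 76 is the wrong sample size; it reproduces and is not in question. The change should be made, but the trial's validity does not depend on it.

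**What to change.** Prespecify the baseline score of each outcome as a covariate in its analysis, whatever the baseline p-values. Either form will do:

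- ANCOVA at each follow-up, with group and baseline score; or
- one model per outcome in SPSS MIXED, with the three follow-up scores as responses and group, visit, group-by-visit, baseline score and baseline-by-visit as fixed effects. This also uses partly missing follow-up.

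Delete the rule that adds covariates after a significant baseline test, and report baseline characteristics descriptively. Any other covariates should be named in advance for their expected prognostic value. State in the Sample size section which SD d = 0.7 refers to. Which follow-up is primary is a separate question that this change does not settle.

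The cost is revised analysis wording and slightly different syntax in the software already named. No new data, visits or participants are needed.

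### Two primary outcomes are each tested at three follow-ups at p < 0.05 with no primary test named, and the sample size supports one unadjusted BSQ comparison but gives no basis for the TFEQ

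*Protocol article*

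**What the plan says.** - **Outcomes, Primary outcomes:** two instruments stand under this heading, the BSQ (a summed total) and the TFEQ-R21. Of the latter the text says: "Three dimensions of eating behavior are assessed: cognitive restriction, uncontrolled eating and emotional eating". It does not say whether these are analysed separately or as one score.
- **Outcomes, Secondary outcome:** "Self-compassion levels: the Self-Compassion Scale (SCS) will be used".
- **Statistical analysis:** primary and secondary outcomes are tested by a group-by-time interaction in a repeated-measures general linear model. "Separate analyses will be conducted for each follow-up point: from baseline to the end of the 8-week intervention, from baseline to 3 months", and likewise to 6 months. The decision rule is: "Differences will be considered statistically significant at p < 0.05". No time point or outcome is ranked above another.
- **Sample size:** 76 women, 38 per group, including 10% for losses. "This calculation considered a power of 80%, a significance level of 5% and a Cohen’s d of 0.7". The comparison to be powered is "a minimal difference in the body dissatisfaction averages and self-compassion levels between the intervention and control groups".

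**The concern.** Two things do not fit together.

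First, the sample size is built on a single comparison at 5%, while the analysis makes several primary comparisons, each at 5%, and says nothing about which of them decides the trial. If any significant result may be reported as success, the risk of a false claim among the primary results is well above 5%. The Discussion section adds to this: it expects the 3- and 6-month data to show which approach works better, so the later time points will carry claims too.

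Second, the outcomes in the sample-size paragraph are not the primary outcomes. One of the two named there is secondary, and one of the two primaries is absent. A reader cannot tell what power the trial has for eating behaviour, although both the main objective and the hypothesis include it.

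**Working it through.** **1. The plan's own figure.** Inputs from Sample size: d = 0.7, power 80%, significance 5%, 10% losses; allocation 1:1 from Randomization. Sidedness is not stated; two-sided is assumed.

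- Two-sample t-test: n = 33.02 per arm, rounded up to 34.
- Losses: 34 / 0.9 = 37.8, rounded up to 38 per arm, 76 in total. The stated figure reproduces.
- A one-sided test would need only 26 per arm before losses and does not reproduce it.
- Power with 34 evaluable per arm at two-sided 5%: 81%.

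**2. Number of primary tests.**

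- One TFEQ score: (1 BSQ + 1 TFEQ) × 3 follow-ups = 6.
- Three TFEQ dimensions: (1 BSQ + 3 TFEQ) × 3 follow-ups = 12.

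**3. Chance of at least one false positive, each test at 0.05.** Under independence this is 1 − 0.95^k. The documents give no correlations. The last column therefore assumes 0.2-0.7 between outcomes and 0.5-0.8 between time points, and simulates multivariate normal test statistics whose correlation is the product of the two.

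| Reading | k | Independent | Assumed correlations |
|---|---|---|---|
| BSQ + one TFEQ score, three times | 6 | 1 − 0.95^6 = 26.5% | about 16-23% |
| BSQ + three dimensions, three times | 12 | 1 − 0.95^12 = 46.0% | about 24-41% |

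Even if week 8 alone were taken to count, one TFEQ score gives 1 − 0.95^2 = 9.8% and three dimensions give 1 − 0.95^4 = 18.5%, under independence.

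**4. Power for the TFEQ.** No TFEQ effect size is given. With 34 per arm at an unadjusted two-sided 5%, over an assumed range:

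| d on TFEQ (assumed) | 0.3 | 0.4 | 0.5 | 0.6 | 0.7 |
|---|---|---|---|---|---|
| Power | 23% | 37% | 53% | 68% | 81% |

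**5. Power if 5% is split between two primaries at week 8.** At alpha = 0.05 / 2 = 0.025, d = 0.7 and 34 per arm, power is 72%. This takes d as applying to the contrast tested. The planned group-by-time test on two time points is a comparison of changes. If d = 0.7 is in raw-score SD units, the standardised effect on change is 0.7 / √(2(1 − ρ)), where ρ is the baseline-to-follow-up correlation (not given):

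| ρ (assumed) | d on change | Power at 0.05 | Power at 0.025 |
|---|---|---|---|
| 0.3 | 0.59 | 67% | 56% |
| 0.5 | 0.70 | 81% | 72% |
| 0.6 | 0.78 | 89% | 82% |
| 0.7 | 0.90 | 96% | 92% |

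The 81% in step 1 rests on the same condition.

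**The case against.** **Detail may sit elsewhere.** A journal article condenses the full protocol, and multiplicity rules are often left to an analysis plan. The main objective also mentions eight weeks, which might point to week 8. This stands only as a limit on what may be called missing. The article itself fixes a flat 0.05 rule for separate tests at three follow-ups, and the eight weeks reads as the length of the intervention; the analysis section does not use it to select a time point. The mismatch between the sample-size outcomes and the primary outcomes is stated text, not omitted detail.

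**Twelve tests is an inference.** This stands. The text says that the dimensions are assessed, not that they are tested separately, and it also speaks of a higher score in the singular. Against that, it gives a rule for a BSQ total and for an SCS total but none for a TFEQ total. The fair range is 6 to 12.

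**Independence is implausible.** This also stands: repeated scores from the same women are correlated. The correlated ranges are the more realistic ones, and they still exceed 5% throughout.

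**A stronger reading does not hold.** A reader might infer that the 80% power fails for both primaries. For BSQ it does not: 76 reproduces and gives 81% for one unadjusted test. For the TFEQ, power is unsupported, not shown to be low; it would be 81% if its d were 0.7. A reader might also take the hypothesis to require success on both constructs and quote a joint power of 66-70% (each at d = 0.7, outcome correlation 0-0.5). The document does not state that rule, gives no TFEQ effect, and gives no ρ, on which that figure depends strongly: with independent endpoints and a raw-score d, it is 0.67² = 45% at ρ = 0.3 and 0.96² = 92% at ρ = 0.7.

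**Conclusion.** The point holds in this form. The protocol makes 6 to 12 primary tests, each at p < 0.05, without saying which one decides the trial, so 5% is a per-test level only. The excess is material on either count: at least about three times the nominal level even with strongly correlated tests (16% against 5%). The exact size rests on assumed correlations.

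The sample size is arithmetically sound for one unadjusted, two-sided BSQ comparison at d = 0.7. It names a secondary outcome beside BSQ and leaves the second primary without any basis. The documents do not support saying that power is below 80% for BSQ as a single test, or that it is known to be inadequate for the TFEQ.

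This should be settled before any comparative data are seen. The Data management section allows an interim analysis for scientific meetings, with results open to all authors, so the deciding test could otherwise be picked after looking.

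**What to change.** 1. In Statistical analysis, name one primary test: BSQ, group-by-time from baseline to the end of the 8-week intervention, two-sided 5%.
2. Test the TFEQ at week 8 only if BSQ is significant. State whether it is one score or three dimensions; if three, apply Holm across them.
3. Treat SCS and all 3- and 6-month results as secondary, reported with confidence intervals.
4. In Sample size, remove self-compassion and state that the 80% power applies to BSQ at week 8 only.

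**Cost:** an amendment and matching registry wording; no extra participants. The TFEQ and the later time points lose stand-alone confirmatory status. This is a real concession, because eating behaviour is in the main objective.

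**If both primaries are to be kept at week 8:** use Holm or Bonferroni, with 0.025 as the first threshold, and restate power as about 72% for an outcome with d = 0.7 on the tested contrast and 34 evaluable per arm. Say that this assumes d is in change-score units or a baseline-to-follow-up correlation of about 0.5, and give an effect-size basis for the TFEQ. On the same assumption, restoring 80% per test at 0.025 needs 41 evaluable per arm; 41 / 0.9 = 45.6, so 46 per arm, or 92 women. If the TFEQ is kept as three dimensions, the split is over more than two tests and power falls further (63% at 0.05 / 4).
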